### Study setting

There are multiple participation sites around the UK (including Scotland, Wales and England). These are located in secondary or tertiary care clinics for movement disorders and/or cognitive disorders. All study visits occur at the trial site, unless visit 6 is undertaken remotely.

### Patient and public involvement

NORAPS was proposed in outline at the foundation of the Cambridge Centre for Parkinson-Plus (CCPP). The CCPP established a panel of patients and relatives with lived experience of PSP and corticobasal syndrome, to discuss and review new research proposals, their aims, scope and participant-facing documentation. The group was led by a senior research nurse who is not part of the NORAPS team. The NORAPS draft protocol and documentation were reviewed and revised in response to feedback from people with lived experience of PSP and CBD. This panel did not include participants or relatives of participants in the trial. The study progress has been presented at annual meetings of the Cambridge Neuroscience Clinical Trial Unit Annual Events 2022, 2023 and 2024, which include trial participants and individuals with lived experience of dementia and neurodegenerative disease.

#### Blinding

This is a crossover, double-blind, placebo-controlled, fixed-dose design. Participants receive 8 weeks of atomoxetine and 8 weeks of placebo, with the order of treatment randomised. Participants, their informants (and other carer/family members) and the clinical trial team (including the PI, chief investigator, trial manager and study nurses) are blinded to the treatment allocation to minimise the risk of bias. Site pharmacies will be unblinded.

Eligible consented patients will be randomised on a 1:1 basis to one of the two trial crossover arms using a web-based randomisation process with the randomisation schedule consisting of blocks of random length (2 or 4) to ensure balanced randomisation during the course of the trial.

At randomisation, an unblinded email is sent to the local site pharmacy for the patient, who, on receipt of a trial prescription, prepares the relevant treatment pack prior to the participant receiving their medication. A blinded email is sent to the trial and local research teams, confirming that randomisation has occurred.

Due to potential sedimentation in oral solutions, which may affect the appearance of the IMP (but not safety), there are additional mitigating actions to maintain blinding. The IMP bottles are dark. Participants are notified that sedimentation ‘opacity’ may occur and is not a risk to them and does not need to be reported to the study team. When unused IMP is returned to the study site at the end of each treatment phase, it is returned in opaque envelopes. If the receiving staff member is informed of sedimentation or opacification, they record this but do not report the information to other local site team members or to the lead site during the conduct of the study. If enquiries need to be made about IMP appearance, a consultant neurologist has been identified, who is not part of the main study team, to field initial enquiries. All incidences of potential or perceived unblinding will be recorded and monitored in a way that does not lead to sharing potential unblinding information with any other members of the study team.

Members of an independent data monitoring committee (DMC) will review blinded data on a regular basis to enable safety monitoring. If they have concerns, they can request unblinded information from the treatment group. This unblinded information is not disclosed to other members of the team. The DMC will comprise two external clinical experts and an independent statistician, as well as the trial statistician and statistical lead.

For the purposes of study blinding, active IMP (atomoxetine) and matched placebo will be dispensed in matched bottles and labelled with blinded Annex 13-compliant labels (approved by the Medicines and Healthcare products Regulatory Agency (MHRA)). Assembly activities (ie, rebottling in order to blind trial medication) will be undertaken by local pharmacy teams out of sight of any blinded site staff or the patient/informant/carer, friend or family member. The product will be dispensed by and returned directly to pharmacy so that research staff do not see the bottles or contents, thereof, to minimise any potential risk of unblinding.

An investigator or physician may unblind only in the case of (1) a medical emergency or in the event of a serious medical condition, and (2) when knowledge of the investigational product is essential for the clinical management or welfare of the participant. If a suspected unexpected serious adverse event is reported, delegated members of the clinical trial unit (not including the direct trial team) will be able to unblind a participant to enable expedited reporting to the regulatory agencies.

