An estimate (with inferences) of the effect of atomoxetine on cognition and behaviour, specifically whether atomoxetine is effective in reducing apathy, impulsivity and improving behavioural control.The influence of genetic variations in the NET gene in predicting response to atomoxetine.The influence of CYP2D6 on atomoxetine metabolism (nuisance variable) in predicting response to atomoxetine and in affecting pharmacokinetic measures.Whether volumetric differences in the LC are predictive of atomoxetine response and whether participants with significant behavioural impairments at baseline have significantly different LC volumes than participants with less severe impairments.To develop a predictive model of atomoxetine response by cross-validation, combining clinical and imaging features.^26^

The primary efficacy endpoint will be evaluated by comparing the cognitive and behavioural changes following 8 weeks of daily atomoxetine versus 8 weeks of placebo, as measured by the Apathy-Impulsivity composite subscore from the CBI-R. This subscore includes the following CBI-R subscales: abnormal behaviours (6 items), ‘euphoria’ mood items (2 items), stereotypic and motor behaviours (4 items), eating habits (4 items) and motivation (5 items).^50^,^52^ Owing to this being a crossover trial where participants act as their own control, the effect size is calculated within individuals between treatments (drug and placebo).

The estimate of efficacy will be through a general linear model, with the assumption of normally distributed errors. The model-dependent variable will be the difference in CBI-R between the control period and the intervention period. The model will include recruiting site (as a random effect) and the difference in CBI-R baselines. Other genuine baseline values (ie, where there can be an observable difference between the control and intervention baselines) will be considered for prognostic variables and included in the model. The intercept estimate from the model then serves as the estimate of efficacy. This will be presented with 95% CIs, and a two-sided 5% significance level will be set.

The primary analysis will follow the Intention-to-Treat principle. All participants who complete visit 2 (dose initiation) will be included, as far as data allows, irrespective of actual intervention or dosage received.

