Missing values will be dealt with using the following strategy. If the degree of outcome data missing is less than 2.5%, only a complete case analysis will be used. In the case that more than 2.5% and less than 50% of data are missing initially, any missing questionnaire item data will be imputed according to any questionnaire-specific approaches; for example, if one item is missing, the mean of those completed may be used. In the absence of specific guidelines, where individual items are missing, an approach will be discussed and agreed on with the study DMC. When entire questionnaire data are missing, a multiple imputation approach will be used to impute the between-period differences. In the event that more than 50% of the entire questionnaire outcome data are missing, an approach will be discussed and agreed on with the DMC, including, depending on the pattern of missing data, reducing the study to a parallel-arm analysis using first-period data alone.

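### The DMC is called independent but includes the trial's own statisticians, may see unblinded data, and agrees two contingency rules for missing primary-outcome data with no requirement that this come first

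*Protocol article*

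**What the plan says.** The Blinding section of the protocol article sets up the committee: "Members of an independent data monitoring committee (DMC) will review blinded data on a regular basis to enable safety monitoring". On access it adds: "If they have concerns, they can request unblinded information from the treatment group". On confidentiality: "This unblinded information is not disclosed to other members of the team". On membership: "The DMC will comprise two external clinical experts and an independent statistician, as well as the trial statistician and statistical lead". Earlier in the same section, the article states that participants, informants and "the clinical trial team (including the PI, chief investigator, trial manager and study nurses) are blinded to the treatment allocation".

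The missing-data paragraph under Data analysis gives the committee a second task. Where individual questionnaire items are missing and there is no specific guideline, "an approach will be discussed and agreed on with the study DMC". Where more than 50% of whole-questionnaire outcome data are missing, the approach is again to be settled with the committee. One option named there is "reducing the study to a parallel-arm analysis using first-period data alone".

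**The concern.** A monitoring committee may look at data by treatment because its members stand outside the conduct and analysis of the trial. Here the stated membership does not match the stated independence. The article describes one of the three statisticians as independent, which implies that the other two are not. It lists those two as members, not as attendees at open sessions.

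The second difficulty is the combination of tasks. A body that may hold unblinded information also agrees parts of how the primary efficacy outcome is computed. If the information comes first and the agreement second, the choice is no longer demonstrably made without knowledge of allocation. What is at stake is the credibility of the primary CBI-R result in that event. Blinded decision-making cannot be restored once allocation has been seen.

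**Working it through.** The point concerns governance and the plan gives no figure for it, so the check sets the statements side by side and then asks how likely each route is.

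**1. Membership (Blinding).** Two external clinical experts + one independent statistician + the trial statistician + the statistical lead = 5 members. Of these, 3 are external and 2 belong to the trial. This conflicts with the word independent in the same section.

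**2. Where the barrier lies (Blinding).** Unblinded information is kept from other members of the team. As worded, the barrier runs around the committee. No closed session or exclusion is stated for its two trial members. Elsewhere the section does draw such a line: for a suspected unexpected serious event, unblinding goes to delegated clinical trials unit staff outside the direct trial team.

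**3. What the committee agrees (Data analysis).** The rules for missing outcome data are:

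| Situation | Rule | Committee role |
|---|---|---|
| Less than 2.5% missing | Complete-case analysis | None |
| 2.5% to 50%, items missing, questionnaire guideline exists | Questionnaire's own rule | None |
| 2.5% to 50%, items missing, no guideline | To be agreed | **Yes** |
| 2.5% to 50%, whole questionnaire missing | Multiple imputation of between-period differences | None |
| More than 50% of whole questionnaires missing | To be agreed; may become first-period only | **Yes** |

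The role is confined to two contingencies. Neither comes with a requirement that it be settled before unblinded review or database lock.

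**4. How likely each contingency is.** The Sample size section anticipates 10–15% dropout with a recruitment target of 84. That is 0.10 × 84 = 8.4 to 0.15 × 84 = 12.6 participants, well above 2.5% (2.1 participants) and far below half (42). If dropout is taken as a stand-in for missing outcomes, the trial would fall in the 2.5–50% band, where the item-level contingency sits. For the other contingency, assume that losses are independent between participants. The chance of more than 42 of 84 missing is then P(X > 42), X ~ Binomial(84, p):

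- p = 0.15: about 1 × 10⁻¹⁴
- p = 0.30 (twice the upper anticipated rate): about 4 × 10⁻⁵

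The first-period fallback is therefore very unlikely to be reached. The item-level contingency is the one that could arise in practice, if the CBI-R has no guideline of its own for missing items. The article does not say whether it has one.

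**5. The chain that must hold for harm.** A safety concern arises; the committee requests unblinded information; that information reaches people who take part in the missing-data decision; and that decision is still open. The article does not prevent this sequence, but it does not make it routine either.

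**The case against.** The strongest reply is that the committee's default is blinded safety review, that unblinding needs a concern, and that no interim efficacy analysis is described. Efficacy is assessed only after the last patient's last dose and data lock. Closed-session rules normally sit in a charter, which a condensed article may omit. All of this stands and limits the size of the point. It does not remove it, because the article does not simply leave out the arrangements. It states a membership and a barrier, and an unseen charter would have to override both.

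A reader might infer four stronger things, which the documents do not support:

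- **That the trial statisticians are unblinded.** They are not named among the blinded roles, but that list opens with the word including and is not exhaustive. The article also does not say which committee members receive unblinded information.
- **That the committee or its statisticians choose the covariates.** The article says that baseline values "will be considered for prognostic variables and included in the model", names no decision-maker and gives the committee no part in it. A covariate list is commonly left to the SAP, which is not shown.
- **That the committee agrees the missing-data method as a whole.** It agrees two contingencies; the other rules are fixed.
- **That type I error rises to a stated level.** Taking the better of two two-sided 5% tests gives 9.75% if they are independent, 9.1% at a correlation of 0.5 and 8.3% at 0.7. The arithmetic is right, but it assumes a free choice after seeing both results, and the correlations are assumed. In this plan the first-period option opens only above 50% missing and depends on the pattern of missing data, not on a result.

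**Conclusion.** The point holds as a conditional risk. Within one section, the article contradicts itself on the committee's independence. It also allows that committee both to obtain unblinded information and to agree two parts of the primary-outcome missing-data handling, in no stated order. If an unblinded request came before those choices were fixed, they could be made by people who know allocation.

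No realistic effect on type I error can be calculated from the documents. One contingency is very unlikely at the anticipated dropout, and the effect of an item-level rule cannot be sized from what is given. The conclusion assumes that no charter or SAP, neither of which is shown, already separates the two trial statisticians or fixes the rules blind. This is a worthwhile correction of wording that reduces a risk of bias. It is not a defect that invalidates the primary analysis.

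**What to change.** 1. **Membership.** Limit the committee to the three external members. The trial statistician and statistical lead attend open sessions only, without a vote and without access to unblinded information.
2. **Missing-data rules.** Remove the committee's agreement from the missing-data paragraph. Have staff blind to allocation fix the rule for missing CBI-R items without a guideline, and the rule for more than 50% of whole questionnaires missing. Both should be recorded before any unblinded data are released and before database lock.

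The cost is wording in the committee's charter and the SAP. Sample size, visits and data collection do not change. According to the article, 76 participants had entered treatment by 16 May 2025 and recruitment was expected to finish in autumn 2025, with efficacy assessed only after data lock. On that timetable the change could still be made in time, provided that no unblinded request had come first.

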#### Intervention

Atomoxetine is an NA reuptake inhibitor, currently licensed for the treatment of ADHD in children, adolescents and adults. The 40 mg dose is at the lower end of the clinical dose range (40–100 mg). This dose of atomoxetine has also been well tolerated in psychopharmacological studies in older adults and people with sleep apnoea and PD.^21 22 24^ Doses up to 100 mg/day have been used in trials with mild cognitive impairment or for PD in older adults and were well tolerated.^44^

Atomoxetine liquid solution is commercially available in a 4 mg/mL formula. It is marketed with the brand name Strattera. It is clear and colourless. In addition to atomoxetine, each millilitre also contains 32.97 mg of sorbitol, 0.8 mg of sodium benzoate, 9.8 mg of propylene glycol and 2.64 mg of sodium. Placebo liquid is produced by Guy’s and St Thomas’ NHS Foundation Trust Pharmacy and has been analysed and deemed to adequately resemble the atomoxetine solution in appearance, colour, viscosity and taste. Both atomoxetine and placebo are packaged in identical 100 mL amber glass bottles, with a 28 mm polypropylene tamper-evident, child-resistant screw cap.

### Outcomes

The primary outcomes include:

Safety of atomoxetine will be determined from the number of participants with serious adverse events (SAEs) and adverse events (AEs) leading to discontinuation. Tolerability will be assessed by the review of the list of all AEs and reactions (including serious) experienced by participants during the trial.Efficacy of atomoxetine against the challenging behaviours quantified by a subscale of the CBI-R.^34^ This subscale includes the following CBI-R items: abnormal behaviours (6 items), ‘euphoria’ mood items (2 items), stereotypic and motor behaviours (4 items), eating habits (4 items) and motivation (5 items).

The secondary outcome measures include:

CGI-C.^29^CBI-R Motivation Subscore.^34^CAMQUAIT.^30^CAARS—patient’s and carer’s versions.^31^HADS.^32^RBANS.^33^PSP-QoL.^5^PQoL Carers.^6^

The exploratory outcome measures include:

7T MRI (or lower field MRI for sites without 7T MRI facility).Genetics (DNA for assessment of variations in the CYP2D6 and NET genes).MoCA.FAB.Performance on the SST, quantified primarily by Stop-Signal-Reaction-Time (integration method), with additional subject-specific values for go-reaction times, attentional and trigger failures derived from the dynamic models of change analysis method.^45 46^PSPRS full scale (28 items).^35^PSPRS modified scale (14 items).^47^PSP-CDS.^36^Levels of atomoxetine in blood.12-lead ECG abnormalities, heart rate and blood pressure.

### Sample size

A total of 74 participants (37 within each sequence) were estimated a priori to provide 80% power, with statistical significance set at the two-sided 5% level, to detect an effect size of one-third. That is, a difference in mean outcome between treatments of one-third the size of the SD of the individual differences. Given the crossover design, the effect size is calculated within individuals between treatments. A dropout rate of approximately 10–15% is anticipated (based on previous studies in PSP); therefore, the target recruitment is 84 people with PSP (each with an informant). However, the number of patients recruited to the trial may be adjusted according to the actual attrition rate if necessary. Patient participants who are randomised but do not start the treatment phase will be replaced.

### Retention

The criteria for a participant to leave the study are:

Participant’s decision.Confirmed pregnancy.A serious adverse reaction (SAR).Decision of the physician responsible for a study participant, on appropriate medical grounds (eg, individual AEs, illness, protocol violations, significant suicidal risk or new information gained about study procedures).

If a participant chooses to discontinue the study drug phases, they will continue to be followed up as closely as possible to the follow-up schedule defined in the protocol, provided they are willing. They are invited to continue follow-up in the trial even though they no longer take the study drug. If the reason for withdrawal relates to participant safety, a follow-up safety consultation (phone call or visit, depending on severity) is conducted within the week after the participant stops the treatment. NCTU is informed of the treatment discontinuation in writing using the appropriate trial documentation.

If a participant chooses to discontinue their study drug and is willing to be followed up, but in a limited manner, they are invited to participate in a close-out visit for safety (AEs) prior to withdrawal. The safety close-out visit may consist of a telephone call at an agreed time, approximately 2 weeks after the last dosing, during which any AEs will be collected if the participant is still willing. Full withdrawal from the trial will take effect from that time. If, in addition to withdrawal from trial treatment, the participant also expresses the view that they no longer wish to be followed up, this view will be respected, and the participant will be withdrawn entirely from the trial.

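### Continued follow-up is promised only when the participant chooses to stop study drug; read literally, SAR-triggered and physician-decided exits lose outcome data, which weakens the ITT analysis

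*Protocol article*

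**What the plan says.** Protocol article, Retention. The list headed "The criteria for a participant to leave the study are" has four entries: the participant's own decision, confirmed pregnancy, an SAR, and a decision of the responsible physician. The SAR entry carries no condition. The physician entry gives examples, among them "individual AEs, illness, protocol violations, significant suicidal risk".

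The same section then describes follow-up:
- Full schedule: "If a participant chooses to discontinue the study drug phases, they will continue to be followed up as closely as possible", provided they are willing.
- Limited follow-up: a close-out safety contact, followed by full withdrawal. This route also starts from the participant choosing to stop.
- Safety-related withdrawal: "If the reason for withdrawal relates to participant safety, a follow-up safety consultation (phone call or visit, depending on severity) is conducted within the week" of stopping treatment. No outcome assessment is mentioned in that sentence.

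Protocol article, Data analysis. The primary analysis is intention-to-treat among all who complete visit 2, "irrespective of actual intervention or dosage received", but only to the extent that the data permit. The dependent variable is the within-person difference in CBI-R between the two periods. With less than 2.5% of outcome data missing, only complete cases are analysed. Between 2.5% and 50%, missing between-period differences are multiply imputed.

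**The concern.** An intention-to-treat estimate that disregards what was actually taken needs outcomes measured after treatment stops. The Retention section draws the right distinction between stopping drug and leaving the trial, but writes it out only for stops that the participant chooses. If a site applies the list as written, a participant with an SAR, or one taken off by a physician, has no further outcome visits.

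The crossover makes this costlier than in a parallel trial. The outcome is a difference between periods, so an exit before the second period's 8-week assessment removes the participant's contribution altogether. An exit in the first period also loses the whole second period.

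These exits may be informative. An SAR is by name attributed to the drug, although causality is judged blind, and the Outcomes section counts adverse events leading to discontinuation in the primary safety outcome. If such participants are then handled like those who stayed, the estimate drifts from the effect in everyone who started towards the effect in those who tolerate the drug.

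**Working it through.** **1. The plan's own figure.** Sample size gives 74 evaluable participants for 80% power, two-sided 5%, and an effect of 1/3 of the SD of within-person differences.
- Normal approximation: n = ((1.960 + 0.842) / (1/3))² ≈ 70.6, so 71.
- Noncentral t: n = 73, and power at 74 is 80.8%. The figure reproduces.
- Recruiting 84 implies a dropout of 1 − 74/84 = 11.9%, inside the stated 10–15%.
- At 15% loss, 84 × 0.85 = 71.4; power with 71 is 79.1%.

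Lost numbers therefore cost little power. The question is bias.

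**2. Who is promised outcome visits.** Setting the exit list against the follow-up text:

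| Route | Scheduled outcome visits stated? |
|---|---|
| Participant chooses to stop drug, willing | Yes |
| Participant chooses limited follow-up | No; safety contact, then withdrawal |
| SAR | Not stated |
| Physician decision (adverse events, protocol violations and others as examples) | Not stated |

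**3. Illustration of bias.** The documents do not split exits by reason, so every input here except 1/3 is an assumption. Let completers have the planned effect of 1/3 SD. Let a share p exit by SAR or physician decision, with a true mean difference of k × 1/3. Suppose the analysis treats them like completers.

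- Effect in all who started = (1/3)[(1 − p) + pk]
- Absolute overstatement = (1/3)p(1 − k)
- Relative overstatement = 1/[(1 − p) + pk] − 1

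| p | k = 0.5 | k = 0 | k = −1 |
|---|---|---|---|
| 5% | 0.008 SD (2.6%) | 0.017 SD (5.3%) | 0.033 SD (11.1%) |
| 10% | 0.017 SD (5.3%) | 0.033 SD (11.1%) | 0.067 SD (25.0%) |
| 15% | 0.025 SD (8.1%) | 0.050 SD (17.6%) | 0.100 SD (42.9%) |

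Here k = 0 means that nothing of the drug effect remains after stopping, and k = −1 means that leavers do worse by as much as completers gain. The 10% and 15% rows are upper bounds on p, because they count the whole anticipated all-cause dropout as this kind of exit.

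**4. Scale.** The standard error of the mean difference at n = 74 is 1/√74 = 0.116 SD. At p = 5% and k = 0 the shift is 0.017/0.116, about one-seventh of a standard error.

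**The case against.** The strongest reply is that nowhere does the article say outcome collection stops after an SAR or a physician's decision. The exit list begins with the participant's own decision, and the next paragraph keeps exactly those participants in follow-up if they are willing. The list heading therefore cannot by itself show that data end. The safety-consultation sentence sits inside the continued-follow-up paragraph and is timed from stopping treatment, so it may well be an additional contact and not a substitute. The full protocol (V.3.1), which is not shown, may settle the matter.

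Several further points stand and limit the concern:
- A reader might infer that any adverse event or protocol violation removes a participant. The text does not support this: both are examples under a discretionary decision on medical grounds. Only the SAR entry is unqualified.
- A reader might infer that imputation will draw these participants from completers. The imputation model is not stated in the article, and participants followed after stopping drug could inform it.
- A higher exit rate on active drug is a reasonable inference, but no figure supports it. The Intervention section describes the 40 mg dose as well tolerated in earlier studies.
- Dropout here has other causes. Current study status attributes seven losses during the supply pause to disease progression or death.

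What does not fall away is that both follow-up routes begin with the participant's choice, and that nothing in the article extends them to the other exits. If wider follow-up is intended, the published wording fails to say so, and the same sentence would put it right.

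**Conclusion.** The concern holds as a weakness in how the intention-to-treat analysis would be delivered. On a literal reading, exits triggered by an SAR or decided by a physician lose later outcome data, including the between-period difference.

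It would be tempting to conclude that Retention contradicts the intention-to-treat statement. The documents do not support that: Retention blurs stopping drug with leaving the study, and the intention-to-treat sentence limits inclusion to what the data permit.

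The size of the bias is unknown. If 5% exit this way, retain no effect and are treated like completers, the overstatement is about 0.017 SD, or 5% of the planned effect. It is smaller if some effect is retained and larger if leavers do worse than on placebo. The 10–15% cases should not be quoted as expected values. Power is hardly affected. This is an inexpensive improvement worth making, not a flaw that invalidates the design.

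**What to change.** Reconcile Retention with Data analysis by treating stopping study drug and leaving the study as two separate events. Leave the clinical triggers and the physician's discretion exactly as they are. State that:

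- after any stop of study drug, whoever decides it, the scheduled outcome visits continue where the participant is willing and the physician sees no safety objection, with the informant-rated CBI-R as the minimum;
- a protocol violation alone does not end outcome collection.

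The wording needed already exists in Retention for participant-chosen stops and only has to be extended.

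The cost is a wording change and a few outcome visits for stopped participants, inside the existing schedule. The benefit is limited by timing: 76 participants had entered treatment by 16 May 2025 and recruitment was due to finish in autumn 2025, so the change reaches only those still in follow-up or yet to be recruited.
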